## 4. REQUEST FOR AMENDMENT DETAILS

### 4.1 Nature of and reason for amendment

We propose three amendments to the project.

1) We wish to amend the inclusion criteria of the project, to allow participation from anyone interested in the study regardless of their depression status (phase two). Previously, participation was restricted to adults with sub-threshold symptoms of depression, who were not receiving depression treatment (phase one). We would like to open up the study to those with full threshold depression, as well as those with any number of symptoms. Undergoing concurrent treatment for depression will also not be an exclusion criterion, because the intervention does not interfere with psychological or medical treatment. This recognizes that participants will be more likely to be in treatment if they have full-threshold depression.

We wish to make this amendment because preliminary analyses of the study show that the Mood Memo emails change self-help coping behaviour, and depressive symptoms to a smaller extent. We hypothesise that the effect on depressive symptoms will be greater for those who are more depressed at the beginning of the study than for those with sub-threshold depression. We think this is probable because effect sizes are typically greater for treatment studies than for prevention studies (Jané-Llopis, Hosman, et al., 2003). Furthermore, there was significant interest in participating from individuals who were already in treatment or who had 'full' depression, and it would be worthwhile investigating whether the Mood Memos had any effects additional to treatment effects.

We plan to analyse the data collected with the changed inclusion/exclusion criteria separately from that already collected in phase one. This is feasible because of the number of participants recruited to date. This will also preclude any suggestion that the trial is being extended to ‘chase’ statistical significance.

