We will continue to advertise the study and recruit participants in the same manner as before (primarily through Google advertising). We will aim for a sample size of 1600 participants in this second phase of the study. This is based on a power analysis indicating that a sample of 393 per condition would give 80% power to detect a small effect size (0.2 standard deviations between conditions) on a continuous outcome measure assuming a correlation of 0.5 between pre- and post-test scores. As approximately 50% of participants in phase one did not complete the post-test assessment, a total sample of 1600 allows for a similar rate of attrition. 1600 participants is a feasible target given that 1336 participants with sub-threshold depression were recruited in phase one.

To clarify, the inclusion criteria will now be:

- a. 18 years or older
- b. Access to the internet at least once per week
- c. Resident of Australia, New Zealand, Canada, Ireland, United Kingdom, USA
- d. Any score on the PHQ-9 depression questionnaire
- e. Informed consent

2) The second change we propose is to send an additional reminder email requesting the participant to complete post- and follow-up assessments, bringing the number of reminders to two. This is because up to 50% of participants did not complete assessments, and the reminder email resulted in about 25% more responses. Therefore, a second reminder may lead to a significantly higher response rate.

3) The third change we propose is to amend the wording of the help-seeking question asked at mid-point, post intervention and follow-up. This is so that we can collect more specific information about treatments received by participants. The question will be changed from:

"Have you visited a health professional (e.g. doctor, counsellor, psychologist) to help deal with your depression during the past [3 weeks] / [6 weeks] / [6 months]? (Yes/No)"

to:

"Which treatments for depression have you received from a professional during the past [3 weeks] / [6 weeks] / [6 months]? (multiple responses allowed)

• Nothing, just the consultation

• Psychological therapy

o Acceptance and commitment therapy

o Behaviour therapy

o Cognitive behaviour therapy

o Dialectical behaviour therapy

o Family therapy

o Mindfulness-based cognitive therapy

o Problem solving therapy

o Psychoanalytic psychotherapy

o Supportive psychotherapy or supportive counselling

o Not sure what type

• Medication

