#### **4.3 Possible inconvenience or risks to participants**

There are no changes to the content of the intervention hence no new risks are anticipated. However, there is a risk that participants may think the intervention is a substitute for professional treatment, which could be problematic for those with full depression. This could mean that participants may be less likely to seek professional help if they have not already done so, which could prolong their depressive episode.

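### The amended help-seeking item gives no valid answer to a participant who saw no professional, so help-seeking is no longer measured unambiguously

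*Protocol*

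**What the plan says.** The third change in section 4.1 of the Request for Amendment is to "amend the wording of the help-seeking question asked at mid-point, post intervention and follow-up", in order to get more detail on treatments received.

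- **Phase-one item:** "Have you visited a health professional (e.g. doctor, counsellor, psychologist) to help deal with your depression during the past" 3 weeks, 6 weeks or 6 months, answered Yes or No.
- **Phase-two item:** "Which treatments for depression have you received from a professional during the past" the same periods, with "multiple responses allowed". The printed list has three parts: "Nothing, just the consultation", a set of psychological therapies, and a set of medications. Both sets include an entry for people unsure of the type.

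The new item is introduced with "The question will be changed from", so it replaces the old one. No filter question, skip rule or required-response rule is described.

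Section 4.3 of the same request names a risk of opening the study to people with full depression: "participants may be less likely to seek professional help if they have not already done so".

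**The concern.** The old item sorted every respondent into visited or not visited. The new item asks which treatments a professional gave, so it takes the visit for granted. Nothing on the printed list means that no professional was seen.

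The people left without an answer are those whom the section 4.3 risk is about: participants who have not sought help and may put it off because of the emails. If the item cannot separate them cleanly from people who consulted or who skipped the question, the trial's information on that risk is blurred where it is most needed. The stated purpose of the change is finer detail on treatment, and nothing suggests that losing the negative answer was intended.

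**Working it through.** There is no plan figure to reproduce. The check compares response options and then shows how the two possible errors behave.

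**Step 1. Where each kind of participant lands**

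| Participant | Phase-one item | Phase-two item as printed |
|---|---|---|
| Saw a professional, had treatment | Yes | Ticks a therapy or medication |
| Saw a professional, no treatment | Yes | Ticks the consultation-only option |
| Saw no professional | No | Blank, or ticks the consultation-only option wrongly |
| Skipped the question | Blank | Blank |

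In the phase-one item the last two rows were distinct. In the phase-two item they share a code (blank), or the third row joins the second.

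**Step 2. Non-consulters tick the consultation-only option**

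Let p be the true consultation rate and q the share of non-consulters who tick that option. Neither is in the documents, so all values are assumptions.

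Observed rate = p + q(1 − p).

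With the same q in both arms, observed difference = (p1 − p2)(1 − q).

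For assumed true rates of 30% and 20% (a 10-point difference):

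| q | Observed rates | Observed difference |
|---|---|---|
| 0 | 30% v 20% | 10 points |
| 0.05 | 33.5% v 24% | 9.5 points |
| 0.25 | 47.5% v 40% | 7.5 points |
| 0.5 | 65% v 60% | 5 points |

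The level of help-seeking is overstated in each arm and the difference is pulled towards zero. Both make a reduction in help-seeking look smaller than it is. If q differs between arms, the simple factor does not apply and the direction of the error is not fixed.

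**Step 3. Non-consulters leave the item blank**

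Let s be the true rate and m the share of respondents who skip the item whatever their true answer; again both are assumed.

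Ticked = s(1 − m); blank = 1 − s(1 − m); share of blanks that are skips = m / blank.

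With m = 0.10:

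| True rate s | Ticked (the estimate if blank is read as No) | Blank | Blanks that are skips |
|---|---|---|---|
| 10% | 9% | 91% | 0.10/0.91 = 11% |
| 30% | 27% | 73% | 0.10/0.73 = 14% |
| 50% | 45% | 55% | 0.10/0.55 = 18% |

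With m = 0, reading blank as No is exact. Treating blanks as missing leaves only people who ticked something, and no rate can be estimated. Responses to the printed item identify neither q nor m.

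**The case against.** **The form is not visible.** The request asks for amended questionnaires as attachments (section 5), and these are not in the text at hand. A gate or a none option on the live form cannot be ruled out, and the consultation-only option would make good sense behind a gate. This stands as a limit on certainty. Section 4.1 nevertheless sets out the new wording as the whole replacement.

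**Help-seeking is still recorded.** A reader might infer that it can no longer be measured at all. The documents do not support that. A correct tick still shows professional contact, in more detail than before, and a blank in an otherwise completed survey can be read as No to a fair approximation (step 3).

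**The item is supplementary.** Help-seeking is not among the outcomes named in the executive summary (1.1) or the method (1.3), and section 4.4 of the request deals with the section 4.3 risk through wording in the plain language statement and an email footer. This stands and limits the severity: the depressive-symptom outcomes, randomisation and sample size are untouched.

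**The size is assumed.** No document figure supports any value of q, and small values do little harm. That is why a range is shown.

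Three further inferences are tempting but unsupported:

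- *That treatment status is not collected at baseline.* Current treatment was an exclusion in phase one, so it had to be established before randomisation. The amendment does not say that question is dropped.
- *That the plan will group participants by treatment received after randomisation.* The text says only that "it would be worthwhile investigating whether the Mood Memos had any effects additional to treatment effects" and proposes no such grouping.
- *That comparability with phase one is lost to any effect.* Section 4.1 plans to analyse the two phases separately.

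**Conclusion.** The point holds on the printed wording. A participant who saw no professional has no valid answer and is merged either with people who skipped the item or with people who consulted. Professional help-seeking, and so the reduced help-seeking risk in section 4.3, is no longer measured unambiguously.

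The size depends on unknown behaviour. An assumed true 10-point difference falls to between 9.5 and 5 points for q from 0.05 to 0.5 (same q in both arms). Under 10% skipping with blanks read as No, assumed true rates of 10% to 50% are estimated as 9% to 45%. The conclusion assumes that the live form follows the printed wording, with no filter. It is a cheap improvement of moderate severity and does not threaten the main comparison.

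**What to change.** Keep the phase-one Yes/No question, unchanged, as a gate at mid-point, post-intervention and follow-up, and show the treatment list only to those who answer Yes. Alternatively, add an explicit option such as *I did not see a professional* to the list. Either change separates non-consulters from skipped items and leaves the consultation-only option with its intended meaning. If the live form already has such a gate or option, state it in section 4.1.

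The cost is one extra line on an online form and a few seconds per participant. It should be done before phase-two data collection, because responses to the printed item do not show which blanks or ticks are wrong.

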#### **4.2 Impact on documentation**

The plain language statement will be amended to reflect the change in inclusion criteria and will include a statement about the Mood Memos not being a substitute for professional help (see second paragraph in attachment).

#### **4.3 Possible inconvenience or risks to participants**

There are no changes to the content of the intervention hence no new risks are anticipated. However, there is a risk that participants may think the intervention is a substitute for professional treatment, which could be problematic for those with full depression. This could mean that participants may be less likely to seek professional help if they have not already done so, which could prolong their depressive episode.

#### **4.4 Actions to be taken by researchers to reduce risks**

The plain language statement will be amended to include a statement that the study is not a substitute for professional treatment or diagnosis and professional help is always recommended for depression. Furthermore, the following statement will be repeated in the footer of each Mood Memo email: "This email is not a substitute for professional treatment. Professional help is always recommended for depression."

Other open-access internet-based depression interventions (such as MoodGYM, <http://www.moodgym.anu.edu.au>) take a similar approach to managing the risk of depressed individuals using the program without professional supervision. MoodGYM is a well-regarded and widely used program, and it states the following on its website (<http://www.moodgym.anu.edu.au/welcome/faq#doctor>):

"The information provided throughout MoodGYM is intended for information and skill development purposes only. MoodGYM is not a substitute for seeking diagnosis and treatment from a qualified person. Always consult a medical practitioner or mental health professional if you require a diagnosis or treatment for depression, anxiety or other mental disorders. One reason this is important is that depression is sometimes caused by physical illness or certain medications and a doctor can check these out. Persons under age 16 with depressive symptoms should speak to their parents about seeking professional help for their depression."

#### **4.5 Expected date of implementation of amendment to research**

30-Jun-2011

#### **4.6 Possible affect on funding arrangements**

N/A

#### **4.7 Possible implications for compliance with legislative requirements**

N/A

## **5. ATTACHMENTS**

Copies of the following need to be attached:

- (a) copies of amended surveys, questionnaires or interview questions
- (b) copies of the amended advertisement, plain language statement, and consent form
- (c) any permission or approval letters required as a result of the proposed changes

